### Sample size considerations

This trial is powered to detect reductions in hazardous/harmful alcohol use and risk of depression at 12-month follow-up. The total sample size required to assess these outcomes is 1200 participants. Sample size calculations are based on a cluster randomised design with two active arms and a control arm. The sample size is based on separate analyses of diabetes and HIV clinic populations, showing a difference between the active arms using two-sided tests at α = 0.05 and 90% power. The statistical comparison will be the mean scores of the CES-D and AUDIT at 12-month follow-up. Guided by international and local cluster trials of depression and alcohol use among primary care patients which found ICCs ranging between 0.025 and 0.040 [60, 61], we set the intra-class correlation at 0.030, which is reasonable for outcomes in patients from PHC facilities. Given findings from previous MI [62, 63] and MI-PST [34] interventions, we expect to find a three-unit difference in AUDIT scores at follow-up between the active arms (considered clinically significant) and a between-person standard deviation of 6.5. For this specification with 20 patients per cluster, eight clinics per arm are needed (24 in total). Guided by findings of PST interventions for depression [34, 64], we anticipate a five=unit difference in CES-D scores between the active arms (considered clinically significant) and a between-person standard deviation of 10 units. For this specification, with 20 participants per cluster, seven clinics per arm are needed (21 in total). We will inflate the cluster size of 20 participants to 25 participants per cluster to cater for a worst-case scenario of a 20% attrition rate. Consequently, a sample size of eight clinics per arm (24 HIV and 24 diabetes services in total), with a cluster size of 25 participants (600 unique participants from HIV and 600 unique participants from diabetes clinics) will meet the inference requirements of the trial. During our pilot phase, we recruited participants with depression and those with hazardous/harmful alcohol use in a 2:1 ratio. To ensure we have sufficient power to detect change in alcohol outcomes during the trial phase, we will examine the number of recruited participants who are eligible based on their alcohol use once we have completed recruitment in each site. If necessary, we will augment the sample by recruiting additional participants with hazardous/harmful alcohol use until the required number of 25 is obtained.

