
### Data analysis

#### Primary analyses

With 24 clusters, individual-level analyses of trial outcomes are possible. Mixed-effect linear regression models will be used with clusters and participants specified as random effects to take account of the clustering at the facility level and the repeated measures within participants. We will create separate models for alcohol and depression. The analysis will be intention-to-treat. For cluster RCTs, the dropout of clusters is rare. We will consider using multiple imputations to account for missing responses of participants at follow-up in order to reflect the true overall uncertainty of the estimated effect sizes. The two primary outcomes will be ascertained at three time points for each participant. This repeated measure feature will be used to estimate the intervention effects and 95% confidence intervals for the two primary outcomes at 12 months for three contrasts (the contrast between the Dedicated arm and TAU arm, the contrast between the Designated arm and TAU, and the contrast between the two active arms (Dedicated versus Designated), which will serve as the main comparison). Our primary analysis of outcomes will include adjustment for stratification variables. No adjustment for multiplicity will be made since the trial outcome will be determined by the overall significance of the group (intervention) effect. A similar approach will be adopted to estimate the intervention effects and 95% confidence intervals for the secondary outcomes.

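### The overall three-arm test is made to decide the trial and to excuse multiplicity adjustment, although Dedicated versus Designated is the named main comparison and no rule combines the two primary outcomes

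*Protocol article*

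**What the plan says.** The Primary analyses section plans one mixed model for alcohol and another for depression. From each it estimates three contrasts at 12 months with 95% confidence intervals: each active arm against TAU, and "the contrast between the two active arms (Dedicated versus Designated), which will serve as the main comparison". It then says: "No adjustment for multiplicity will be made since the trial outcome will be determined by the overall significance of the group (intervention) effect".

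Sample size considerations sizes the trial on "showing a difference between the active arms using two-sided tests at α = 0.05 and 90% power". The basis is a 3-unit AUDIT difference and a 5-unit CES-D difference, each at the full two-sided 0.05. No calculation is given for a three-arm overall test or for a contrast with TAU.

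The article does not say whether one or both primary outcomes must be significant. It does not say that the contrasts are interpreted only after a significant overall test.

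**The concern.** With three arms, the overall group effect is a 2-degree-of-freedom test of whether any arm differs from another. It is not a test of Dedicated against Designated. It can be significant only because both active arms beat TAU, and it can miss a real difference between the active arms that the direct contrast would find. The same data could then be reported as positive or negative depending on which sentence of the paragraph is followed. The choice between the two delivery models is the question the Background and Discussion give as the reason for the trial.

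The reason given for the waiver also covers too little. An overall test can protect the contrasts within one model. Here there are two models and so two overall tests, and nothing states how they combine.

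**Working it through.** **Inputs (Sample size considerations).** Two-sided α 0.05, power 90%, ICC 0.030, 20 analysed per cluster, AUDIT difference 3 with SD 6.5, CES-D difference 5 with SD 10. There are three arms of 8 clinics. The correlation between the outcomes is not given, so it is varied from 0 to 0.9.

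**1. The plan's own figures.** Design effect = 1 + (20 − 1) × 0.03 = 1.57. Patients per arm before clustering = 2[SD(1.96 + 1.2816)/difference]².
- AUDIT: 98.7; × 1.57 / 20 = 7.74, rounded up to 8 clinics per arm.
- CES-D: 84.1; × 1.57 / 20 = 6.60, rounded up to 7 clinics per arm.
- 20/0.8 = 25 recruited per cluster; 24 × 25 × 2 = 1200.

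All match the article. The sample size is not in error, and it is the sample size for the active-arm contrast.

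**2. Does the overall test answer the main question?** Variance of a cluster mean = SD² × 1.57/20: AUDIT 42.25 × 0.0785 = 3.317; CES-D 100 × 0.0785 = 7.85. The overall test is F on 2 and 21 df with noncentrality 8 × Σ(arm mean − grand mean)² / variance. The direct contrast is a t test on 21 df. Power is from simulation of cluster means.

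| True state | Noncentrality (AUDIT, CES-D) | Overall test significant | Dedicated v Designated significant |
|---|---|---|---|
| Active arms equal, both better than TAU by 3 / 5 | 8 × 6/3.317 = 14.5; 8 × 16.67/7.85 = 17.0 | 90%, 94% | 5%, 5% (all false) |
| Active arms differ by 3 / 5, TAU midway | 8 × 4.5/3.317 = 10.9; 8 × 12.5/7.85 = 12.7 | 79%, 85% | 88%, 92% |

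In the first row, at least one of the two overall tests is significant in about 98% of trials at correlation 0.5.

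**3. Error rate when no arm differs on either outcome.**

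| Rule | Correlation 0 | 0.5 | 0.9 |
|---|---|---|---|
| Overall test, either outcome at 0.05 | 9.7% | 9.2% | 7.2% |
| Main contrast, either outcome at 0.05 | 9.7% | 9.1% | 7.1% |
| Overall test, both outcomes at 0.05 | 0.3% | 0.8% | 2.7% |

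For independent outcomes the first row is 1 − 0.95² = 9.75%. If both must succeed, the error rate cannot exceed 5% even when one outcome truly responds. Within one outcome, three contrasts tested only after a significant overall test stay at 5%; without that condition they reach about 12%.

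**4. Power at 0.025 (the first Holm step).** Standard error of the contrast = SD√(2 × 1.57/160): AUDIT 0.911, CES-D 1.401. Power (normal approximation) = Φ(difference/SE − critical value):
- AUDIT: Φ(3.295 − 1.960) = 90.9% at 0.05; Φ(3.295 − 2.241) = 85.4% at 0.025.
- CES-D: Φ(3.569 − 1.960) = 94.6% at 0.05; Φ(3.569 − 2.241) = 90.8% at 0.025.

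**The case against.** The contrasts are presented as estimates with confidence intervals, so the overall test could be read as a gate that they must pass. With three arms such a gate does hold 5% within one outcome. Alcohol and depression are also distinct outcomes with their own models, and some statisticians would report each at 5%. Both points stand, and they limit the error-rate part. They do not touch the conflict between the deciding test and the main comparison, which nothing in the article resolves.

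Three stronger readings are tempting but unsupported:
- A reader might count any of the six contrasts as a claim and infer an error rate above 20% (about 22% at correlation 0, 16% at 0.9). That treats the contrasts as ungated claims. The article does not write a gate, but it does say the overall test decides.
- A reader might infer 1 − 0.95⁴ = 18.5% from "The sample size is based on separate analyses of diabetes and HIV clinic populations". That sentence is a basis for sample size. The analysis section does not plan models by disease, and the two populations attend the same randomised facilities, so independence is doubtful.
- A reader might say flatly that 5% is not held. That is true only if success on either outcome is enough, and the article states neither an either-outcome nor a both-outcomes rule.

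**Conclusion.** The point holds in two parts. First, and without condition, the test said to determine the trial outcome is neither the named main comparison nor the comparison the trial was sized on. Under the planning differences this can give a positive trial with no evidence on the main question (about 90% and 94% of trials), or lose power for a real difference between the active arms (79% and 85% instead of 88% and 92%). These figures assume 8 clinics per arm, 20 analysed per clinic in one disease population, and tests on cluster means in place of the mixed model.

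Second, and conditionally, the stated reason does not justify waiving adjustment across two primary outcomes. The error rate is up to about twice nominal if either suffices, and at most 5% if both are required. The fault is that the rule is left open while adjustment is ruled out.

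**What to change.** Delete the waiver sentence. Make Dedicated versus Designated at 12 months the deciding test for each primary outcome, and state how the two combine: either both must be significant at 0.05, or either suffices with Holm over AUDIT and CES-D. Report the two TAU contrasts as secondary, outside the 5% claim.

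If 5% is wanted over all six contrasts, all three contrasts per outcome, including the main one, must pass through that outcome's overall test. Leaving the main contrast ungated and gating only the TAU contrasts gives about 7-7.5% when no arm differs. Gating all three, with Holm applied to the two overall tests, gives about 5% (4.9% and 4.8% at correlations 0 and 0.5) in that null case. A check simulation (300,000 trials) shows a limit: when the active arms are equal and both beat TAU by the planning differences, this procedure gives about 6.5% and 6.0% with contrasts at the Holm level, and 9.7% and 9.1% with contrasts at 0.05. Holding each outcome's overall test and contrasts at a fixed 0.025 keeps it at or below 5%.

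Cost: the change is to wording, but power is affected. Under Holm, first-step power falls from about 91% to 85% for AUDIT and from about 95% to 91% for CES-D, so the stated 90% for AUDIT should be restated. Reaching 90% for AUDIT at 0.025 would need 10 clinics per arm (117 × 1.57/20, about 9.2, rounded up). Requiring both outcomes gives a joint power of about 86% if they are independent (0.909 × 0.946). If HIV and diabetes patients are pooled (40 analysed per clinic, ICC 0.03 assumed), power at 0.025 is about 95.7% and 98.0%, so the article should also say which population the deciding test uses.

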#### Cost-effectiveness analysis

Decision analytical models will be developed to assess intervention costs and outcomes per patient year, from the societal, provider and patient perspective. Discounting will be considered when appropriate. Incremental cost-effectiveness ratios will be used to compare the relative differences between TAU and each active arm. From the provider perspective and within each arm, the cost per patient year will be the product of the utilization of different service units (for example counselling sessions or hospital services) and the unit cost per service. This approach enables uncertainty to be assessed using probabilistic sensitivity analysis on utilization elements and caters for the inherently skewed nature of cost data. From the patient perspective, data collected during patient assessments at baseline and each follow-up will be analyzed using previously established methods [65]. While cost-effectiveness ratios will be computed for each primary outcome measure, QALY measures will allow cost-effectiveness results to be compared with alternative interventions and for allocative efficiency to be assessed.

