## Abstract

**Background:**

In low- and middle-income countries (LMIC), it is uncertain whether a “dedicated” approach to integrating mental health care (wherein a community health worker (CHW) has the sole responsibility of delivering mental health care) or a “designated” approach (wherein a CHW provides this service in addition to usual responsibilities) is most effective and cost-effective. This study aims to compare the effectiveness and cost-effectiveness of these two models of service integration relative to treatment as usual (TAU) for improving mental health and chronic disease outcomes among patients with HIV or diabetes.

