Despite this evidence, uncertainty about how to configure services and resources within the PHC system to allow for the effective integration of mental health counselling has hindered the implementation of integrated mental health and chronic disease services [25, 38]. On one hand, some have shown that basic mental health counselling can be effectively task-shifted to CHWs already working in PHC settings [29, 39, 40], suggesting that resources available in the PHC system can be reconfigured to enable the delivery of new programmes. In contrast, others have argued that CHWs already in the PHC system are overburdened with multiple tasks and therefore unlikely to prioritise the provision of mental health counselling (and may lack the skills and training to be effective), noting that additional human resources are needed for effective integration of mental health and chronic disease services [41–43]. However, health care systems are unlikely to finance additional resources without evidence of the cost-effectiveness of this investment relative to other approaches to service integration [44]. To the best of our knowledge, there has been no research comparing the relative effectiveness and cost-effectiveness of these approaches [29]. Addressing this knowledge gap is critical for guiding decision-making around how to proceed with integrating mental health into chronic disease care within South Africa’s PHC system.

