### Trial objectives

The goal of this trial is to identify an effective and cost-effective approach for integrating mental health counselling into chronic disease care in the Western Cape province of South Africa. The primary objective is to compare the effectiveness of a designated approach (where an existing CHW is tasked with providing mental health counselling in addition to their usual responsibilities), relative to a dedicated approach (where a CHW solely responsible for mental health counselling is added to the chronic disease care team), relative to treatment as usual (TAU) for reducing depression and hazardous/harmful alcohol use.

Secondary objectives include comparing the effectiveness of the interventions for improving chronic disease outcomes (HIV1 RNA viral load for HIV and HbA1c for diabetes), adherence to chronic disease treatment, and health-related quality of life (HrQoL) and exploring potential mediators and moderators of the effects of the interventions on primary outcomes. In addition, we will compare the cost-effectiveness of each intervention alternative from a societal perspective.

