## Discussion

In recent years, there have been several global mental health initiatives to identify and strengthen the core elements of health systems required for integrating mental health counselling into PHC services [21, 25] and on implementing task-shifted mental health interventions into primary care services [33]. Some of these initiatives have advocated for additional staffing resources to enable the delivery of integrated care, while others have used staffing resources already present in the system to deliver these additional services. Yet, uncertainty about which of these approaches to service integration is the most effective and cost-effective has hampered the scale-up of mental health counselling [25, 33]. The proposed study will respond to this question by comparing the relative benefits of these two common approaches to mental health service integration on both mental and physical health outcomes. These findings will advance scientific knowledge in the field of mental health service implementation by identifying a model of mental health service integration that is effective and cost-effective.

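### The planned cost-effectiveness ratios set each active arm against TAU and name no dedicated-versus-designated ratio, although that is the decision the trial is meant to inform

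*Protocol article*

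**What the plan says.** The Cost-effectiveness analysis section of the protocol article fixes the comparators in one sentence: "Incremental cost-effectiveness ratios will be used to compare the relative differences between TAU and each active arm". This is the article's only statement of which arms the ratios compare. The same section plans decision models, probabilistic sensitivity analysis, ratios for each primary outcome, and QALYs. The Economic/costing measures section plans provider and patient costs per patient year in every arm.

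Elsewhere the article frames the economic question as a choice between the two active models:

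- Background, on the knowledge gap: "there has been no research comparing the relative effectiveness and cost-effectiveness of these approaches".
- Discussion, on what the study responds to: "uncertainty about which of these approaches to service integration is the most effective and cost-effective".
- Trial objectives: "we will compare the cost-effectiveness of each intervention alternative from a societal perspective".
- The closing summary of the Discussion says that all participating clusters will be trained in whichever model proves best on effect and cost-effectiveness.

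For effectiveness, the Primary analyses section lists three contrasts and singles out "the contrast between the two active arms (Dedicated versus Designated), which will serve as the main comparison".

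**The concern.** TAU, designated and dedicated are alternatives of which a clinic adopts one. For such a choice, the relevant quantity is the extra cost per extra unit of effect in moving from one option to the next more costly one that is still worth considering. A pair of ratios against a common comparator does not give that quantity, and it can hide the fact that one active arm is dominated by the other.

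The gap falls on the contrast that the trial treats as its main one. The article also expects the two active arms to differ on both axes. The dedicated arm adds one CHW per facility, with excess capacity hypothesised there and economies of scope in the designated arm. The sample size assumes a difference between the active arms of 3 AUDIT points and 5 CES-D points. If the reported economic result were just two TAU ratios, the policy choice would rest on figures that do not settle it. A head-to-head comparison added later would not have been pre-specified.

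**Working it through.** **1. Which contrast the trial was sized on.** Inputs from Sample size considerations: two-sided α = 0.05, power 90%, ICC 0.030, 20 patients per cluster, differences between the active arms of 3 (SD 6.5) for AUDIT and 5 (SD 10) for CES-D.

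- Design effect: 1 + (20 − 1) × 0.030 = 1.57.
- n per arm before clustering: 2 × [SD × (z₀.₉₇₅ + z₀.₉₀) / difference]², which is 98.65 for AUDIT and 84.06 for CES-D.
- Clinics per arm: 98.65 × 1.57 / 20 = 7.74, so 8 (stated 8); 84.06 × 1.57 / 20 = 6.60, so 7 (stated 7).
- Attrition: 20 / (1 − 0.20) = 25 (stated 25). Total: 24 × 25 × 2 = 1200 (stated 1200).

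The figures reproduce and are not in dispute. They confirm that the design is built around dedicated versus designated.

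**2. Why the two ratios are not enough.** Let C₁, E₁ be the extra cost and effect of designated over TAU, and C₂, E₂ those of dedicated, with ratios R₁ = C₁/E₁ and R₂ = C₂/E₂. The step from designated to dedicated is

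(C₂ − C₁) / (E₂ − E₁) = (R₂E₂ − R₁E₁) / (E₂ − E₁).

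This depends on E₁ and E₂ as well as on R₁ and R₂, so the same two ratios can go with different decisions. Net benefit at threshold λ is λE − C.

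**3. Illustrations.** The article gives no costs, QALYs or threshold, so every input here is an assumption, in any currency. Designated is held at C₁ = 100, E₁ = 0.02, giving R₁ = 5,000; λ = 20,000; net benefit of designated = 20,000 × 0.02 − 100 = 300.

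| Dedicated C₂, E₂ | R₂ vs TAU | Dedicated vs designated | Net benefit of dedicated | Preferred active arm |
|---|---|---|---|---|
| 400, 0.04 | 10,000 | 300/0.02 = 15,000 | 800 − 400 = 400 | dedicated |
| 150, 0.015 | 10,000 | costs 50 more, gains 0.005 less | 300 − 150 = 150 | designated (dedicated is dominated) |
| 700, 0.04 | 17,500 | 600/0.02 = 30,000 | 800 − 700 = 100 | designated |

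- Rows 1 and 2 have identical ratios against TAU (5,000 and 10,000) and opposite answers.
- In row 1, picking the lower TAU ratio selects designated, which has the lower net benefit (300 against 400).
- In row 3, both arms pass 20,000 against TAU, but the step between them does not.

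**4. Range.** Keep designated as above and E₂ = 0.04, and vary C₂.

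- The lower TAU ratio picks the arm with less net benefit when C₂/0.04 > 5,000 and (C₂ − 100)/0.02 < λ, that is, 200 < C₂ < 100 + 0.02λ. This gives 200 to 500 at λ = 20,000, 200 to 300 at 10,000, and 200 to 220 at 6,000.
- Dedicated passes against TAU but fails against designated when 100 + 0.02λ < C₂ < 0.04λ. This gives 500 to 800, 300 to 400, and 220 to 240 at the same three thresholds.

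Outside these ranges, these simple readings of the TAU ratios agree with the full analysis.

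**The case against.** The strongest reply is that the article already promises what is needed. The objectives cover every alternative, costs are estimated per arm, and the decision models yield costs and effects for all three arms. Subtracting one arm's increments over TAU from the other's gives the head-to-head increment, exactly as in the illustrations above. This stands. A reader might infer that the economic analysis cannot answer the dedicated-versus-designated question; the documents do not support that. The limitation applies to the two ratios named, not to the data or the models.

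A reader might also infer that TAU is to be the sole comparator. The sentence names just the TAU comparisons but does not rule out others. Still, where the Primary analyses section wants three contrasts it lists three, and here two are named.

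Nor do the documents support saying that a decision-maker would adopt the wrong model. They set no threshold and no rule that the lowest TAU ratio wins or that passing against TAU is enough.

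Comparison with TAU is also legitimate. The abstract's aim is to "compare the effectiveness and cost-effectiveness of these two models of service integration relative to treatment as usual (TAU"), and neither model's value over current care is established. That is a reason to keep these ratios, not to stop at them. Finally, an article may leave dominance rules and net-benefit methods to a fuller plan. Their absence is not the point. The point is the choice of comparators that the article does state.

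**Conclusion.** The point holds as a mismatch between the stated ratios and the stated question. The article specifies two ratios against TAU and omits the contrast that it elsewhere treats as central, and those two ratios do not by themselves rank the active arms. The possible consequence runs both ways: an arm can pass against TAU when its step over the other active arm does not, or the arm with the lower TAU ratio can have less net benefit.

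No size can be derived from the documents. The figures above rest wholly on assumed costs, QALYs and thresholds, and show what is possible rather than what is expected. The sample size, data collection and primary effectiveness analysis are unaffected. The economic comparison sits with the secondary objectives, although the overall goal and the planned training of clinics both depend on it.

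**What to change.** Keep the TAU comparisons and replace the sentence on the ratios with a full incremental analysis of the three arms:

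1. Order the arms by mean cost and identify dominated and extendedly dominated options. Calculate each remaining ratio against the next less costly option still in contention.
2. Always report the dedicated-versus-designated difference in cost and in effect. Give it as a ratio where that is interpretable, and otherwise state which arm dominates.
3. Report incremental net benefit for all three contrasts over a range of thresholds, with its uncertainty. The planned probabilistic sensitivity analysis can supply this.

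The cost is a short change of wording and a little more analysis. No new data are needed, because costs and outcomes are already to be estimated in every arm. The change should be made before the economic analysis begins, so that the head-to-head comparison is pre-specified.
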